## Abstract

**Background:**

It is widely recognized that spiritual care plays an important role in physical and psychosocial well-being of cancer patients, but there is little evidence based research on the effects of spiritual care. We will conduct a randomized controlled trial on spiritual care using a brief structured interview scheme supported by an e-application. The aim is to examine whether an assisted reflection on life events and ultimate life goals can improve quality of life of cancer patients.

**Methods/Design:**

Based on the findings of our previous research, we have developed a brief interview model that allows spiritual counsellors to explore, explicate and discuss life events and ultimate life goals with cancer patients. To support the interview, we created an e-application for a PC or tablet. To examine whether this assisted reflection improves quality of life we will conduct a randomized trial. Patients with advanced cancer not amenable to curative treatment options will be randomized to either the intervention or the control group. The intervention group will have two consultations with a spiritual counsellor using the interview scheme supported by the e-application. The control group will receive care as usual. At baseline and one and three months after randomization all patients fill out questionnaires regarding quality of life, spiritual wellbeing, empowerment, satisfaction with life, anxiety and depression and health care consumption.

**Discussion:**

Having insight into one’s ultimate life goals may help integrating a life event such as cancer into one’s life story. This is the first randomized controlled trial to evaluate the role of an assisted structured reflection on ultimate life goals to improve patients’ quality of life and spiritual well being. The intervention is brief and based on concepts and skills that spiritual counsellors are familiar with, it can be easily implemented in routine patient care and incorporated in guidelines on spiritual care.

**Trial registration:**

The study is registered at ClinicalTrials.gov: NCT01830075

## Background

Spirituality is increasingly recognized as an important domain to include in the care for patients with a life threatening illness [1-5]. In a recent Consensus Conference, spirituality has been defined as the aspect of humanity that refers to the way individuals seek and express meaning and purpose and the way they experience their connectedness to the moment, to self, to others, to nature, and to the significant or sacred [4]. According to reports in the United States and Canada, 50%-90% of cancer patients view religion or spirituality as personally important [6-8]. Religion and spirituality can offer a source of comfort, meaning, control and personal growth to patients who are confronted with a life-threatening disease [9,10]. Spirituality may be especially relevant for patients’ well-being. In a recent systematic review on the relationship between spirituality and well-being in cancer patients, the majority of identified studies observed a positive association between spirituality and well-being [11].

Recommendations from the 2005 National Consensus Project on Quality Palliative Care called for increased efforts to understand patients’ existential needs and to conduct and evaluate interventions to address these concerns [4]. Nevertheless, appropriate, effective, and brief interventions to address spiritual concerns are still lacking. One of the key-elements in these spiritual concerns is the experience of contingency: the experience that something is neither a necessity, nor an impossibility, everything could have been different [12]. Contingency will be experienced when it is problematic to incorporate an event into one’s story of life. The diagnosis of advanced cancer may be such an event. The aim of our study is to examine whether an assisted reflection on contingent life events and ultimate life goals can improve cancer patients’ quality of life.

### The experience of contingency

Cancer patients are confronted with a diagnosis and subsequent treatment that may have a large impact on their life perspective [13,14]. Their life lines are suddenly disrupted, which necessitates a reinterpretation of their lives. This experience is called experience of contingency [12]. Experiences of contingency prompt people to shape a meaningful relation to the situations they are confronted with. Meaningful implies: acting in such a way that it logically and plausibly connects to one’s actions in the past, as well as to desires, wishes and needs for the future [15,16]. In a traditional society, the contingency of action and choice was limited [13], but nowadays people have become individuals with their own personal, biographical story that they have to construct and justify by themselves [17,18]. They increasingly feel obliged to shape their own framework of interpretation for situations they are confronted with. Shaping such a framework of interpretation can be facilitated by the construction of a narrative [19,20]. A narrative configures separate events into an intelligible whole [20]. It creates a temporal coherence whereby a so-called plot links past, present and future to one another and to the personal goals that people pursue. In confrontation with a contingent situation an extra narrative effort is required to construct a new framework of interpretation which fits with one’s ultimate life goals [21].

### Ultimate life goals

In the way people react to the experience of contingency and the stories people tell about their life events, we can decipher the underlying life goals [22]. Personal goals express what people find really important. They are the intrinsic source of human action [20,23]. A distinction can be made between instrumental and ultimate life goals [24]. Instrumental goals refer directly to actions and the way actions are carried out, whereas more abstract goals provide information on the purpose or implications of actions [25]. Instrumental goals can be achieved in order to reach ultimate goals [26]. Unlike instrumental goals, ultimate life goals locate concrete situations in a person’s mental and behavioral framework that forms the core of self-identity [24]. They are irreplaceable in that they give meaning to our lives and without them our lives become meaningless [27]. However, in the course of one’s life, goals that give meaning may change. A reconstruction of the ultimate life goals in confrontation with contingency could assist patients to (re)access their own resources and come to terms with the unexpected aspects of life, ultimately improving their quality of life [28-30].

## Methods/Design

This study primarily aims to answer the following question: does an assisted structured reflection on life events and ultimate life goals of cancer patients improve quality of life? To evaluate the effect of the structured reflection we will conduct a multicenter two-armed randomized non-blinded controlled trial. Previous randomized studies on spiritual interventions in cancer patients have included patients from hospices or palliative care units [31-34]. However, spirituality is not restricted to end of life [35]. Therefore, in this study we will include patients who have been confronted with advanced cancer, but still have a life expectancy of at least half a year. The following inclusion and exclusion criteria apply:

Inclusion criteria

1. Patients ≥ 18 years of age with advanced cancer not amenable to curative treatment.

2. Life expectancy ≥ 6 months.

Exclusion criteria

1. Karnofsky Performance Score < 60.

2. Insufficient command of the Dutch language to fill out Dutch questionnaires.

3. Current psychiatric disease.

Eligible patients will be invited by their treating oncologists and asked to give written informed consent. A baseline assessment will take place in consenting patients, including an evaluation of quality of life and spiritual wellbeing. Within two weeks after the baseline assessments patients will be randomized between an intervention and a control group (care as usual) (Figure 1).

**Figure 1 F1:**
[figure not shown]
Study flow-chart.

Two months and four months after randomization, patients of both the intervention and the control group will complete questionnaires regarding quality of life, spiritual well being, empowerment and health care consumption. In the intervention group we will also conduct a telephone evaluation to examine the satisfaction with the intervention.

Patients declining participation will be asked to answer a few questions by telephone, to explore whether participants and non-participants differ.

### Intervention

We have developed a semi-structured interview model for the interpretation of contingent life events in life stories, based on literature on the experiences of contingency and the importance of ultimate life goals. In this interview we inquire into (a) the life events, (b) ultimate life goals, (c) the interpretation of contingent life events (d) reconstruction of life story. Since 2008 this interview model has been used in various populations, including mentally handicapped people, young people with problem behavior, individuals > 30 years, highly qualified young people in their twenties, Zen meditation trainees, volunteers in hospices, cancer patients, primary school teachers, and asylum seekers [24]. The respondents were from a religious and non-religious background. In all populations, the interviews were evaluated positively by most of the respondents. They did not experience the semi-structured nature of the interview as a drawback and frequently indicated that it was a very special experience to reconstruct their life stories in collaboration with an interviewer. In the experimental arm of our randomized study we will use this interview model for an assisted, structured reflection on contingent life events and ultimate life goals, which will be supported by a newly developed e-application. The assisted reflection is carried out in two consultations with a spiritual counsellor. The counsellor analyses the first consultation in the interim and discusses this analysis with the patient during the second consultation (Table 1).

**Table 1 T1:** Summary of the intervention

**Consultation I**	**Analysis**	**Consultation II**
**Patient and spiritual counsellor**	**Spiritual counsellor**	**Patient and spiritual counsellor**
- Draw a life line	- Analyse life line	- Reflect on life line
- Explicate the most important events	- Analyse important life events	- Reflect on most important events
- Define the most important events	- Analyse life goals	- Reflect on life goals
- Draw a life line for the future	- Define coherence and tension between life goals and life events	- Discuss and reflect on tension and coherence between life goals and life events
- Define life goals		- Reconstruct life story

#### Consultation I

In the first consultation with the spiritual counsellor, the patients draw their lifelines (Figure 2). The patients choose from their life line the three or four most important events and discuss these events with the counsellor. Next the patients draw their future life line and define life goals. In this first consultation, the spiritual counsellors use the interview model with specified questions in a given order. The interview model requires a probing technique, which implies that the spiritual counsellor keeps asking questions to unravel aspects of ultimate life goals as well as different layers in the interpretation of life events. The result of consultation I is a reconstruction of the patient’s life story and the reflection of the patients on this story.

**Figure 2 F2:**
[figure not shown]
**Life line drawn using the e-application.** Looking back at their lives, patients indicate heights and lows.

#### Analysis of consultation I

The analysis of consultation I is performed by the spiritual counsellor and concerns three steps. First, using the e-application, the spiritual counsellor classifies the most important life events identified by the patient as active or passive and positive or negative. An active interpretation implies that the person views the event as an active effort in order to reach his/her own goals. A passive interpretation implies that the event happened to the person in a sense that something befalls you. A positive event means that the event foster's you in your striving to achieve a goal. Negative implies that the event hinders you in your striving to achieve a goal. The positive and negative interpretations relate to three dimensions of human thought and action [24]. These three dimensions are: ‘here and now’, ‘whole life’ and ‘a higher reality’ (Figure 3). Here and now implies that the event is situational; it has an impact on the person in the concrete situation. Whole life implies that the event is existential; it transcends the situational meaning and has an effect on the person's whole existence in time and space. Higher reality implies that the event is transcendental; it transcends the situational and existential meaning and has an effect on the person and his whole view of life.

**Figure 3 F3:**
[figure not shown]
Classification of life events using the e-application.

Second, the life goals that the patient defined in the first consultation are being weighed. Three different dimensions are taken into account: pre-intentional, intentional and meta-intentional [36]. The different dimensions help distinguishing between instrumental and ultimate life goals. The pre-intentional dimension describes instrumental life goals and comprises simple intentional ad hoc decisions such as eating when you are hungry. The intentional dimension describes more awareness for the good and evil in the environment. Finally, the meta-intention stage is where people define very abstract possibilities to transcend the world they are living in [24]. This results in a distinction between direct goals, valuable goals and ultimate goals (Figure 4). In the third and last step of the analysis the coherence between life goals and life events is indicated by the spiritual counsellor (Figure 5). The result of this whole analysis is a framework for observation and interpretation of contingent life events and ultimate life goals.

**Figure 4 F4:**
[figure not shown]
**Visual representation of life goals.** The five most important life goals identified by the patient are categorized as direct goals, valuable goals and ultimate goals.

**Figure 5 F5:**
[figure not shown]
Identification of coherence and non-coherence between life events and life goals.

#### Consultation II

Using the analysis of Consultation I, the spiritual counsellor will summarize the results and present them to the patient in a transparent and organized way. The patient is thus aided during a one-hour session to reflect on his/her own framework for interpretation on a more profound level. Methodologically, this may be regarded as a member-check. However, at the same time the patient will be challenged to creatively respond to the results. The last screen on the e-application is built to be changed by the patients themselves. They discuss with the spiritual counsellor what kind of tension or coherence between life events and life goals can be identified (Figure 5). The patients are challenged to search for (in)coherence in their lives. This may aid patients accommodating their contingent life events [37].

### Endpoints

#### Primary endpoints

Two primary endpoints are distinguished. First, general quality of life as measured with the general quality of life scale of the European Organization for Research and Treatment of Cancer Quality of Life Questionnaire-Core 15 Palliative Care (EORTC QLQ-C15-PAL). The EORTC QLQ-C15-PAL is a shortened version of the EORTC QLQ-C30, which is one of the most rigorously studied and widely used health-related quality-of-life questionnaires in oncology research [38-41].

Second, spiritual wellbeing as measured by the subscale meaning/peace of the Functional Assessment of Chronic Illness Therapy - Spiritual wellbeing 12 (FACIT-Sp12). The FACIT-Sp-12 is a widely used measure and is not restricted to a particular religion and is valid and reliable [42]. The FACIT-sp-12 demonstrates good internal consistency reliability and a significant relation with quality of life in a large, multiethnic sample [43,44].

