### Sample size calculation

The primary aim of our study is to improve quality of life and spiritual wellbeing. We will conduct a mixed design measures ANOVA to detect differences between the control-group and the intervention-group over pre-, post- and follow-up measurement. To detect a small effect (effect size f = .10) with statistical power 80%, alpha 5%, and a correlation between repeated assessments of r = .63, we need a sample of 122 patients. With an expected drop out of 20%, we will include 153 patients.

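### With two primary endpoints and two versions of the primary aim, 122 patients give 5% and 80% together only if one endpoint decides or leads a fixed sequence

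*Protocol article*

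**What the plan says.** The Protocol article gives two versions of what the trial is primarily for.

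- **Quality of life alone.** Methods/Design poses one primary question: "does an assisted structured reflection on life events and ultimate life goals of cancer patients improve quality of life". The aim in the Abstract (Background) and at the end of the Background section's opening part is also quality of life only.
- **Both outcomes.** The Sample size calculation section begins: "The primary aim of our study is to improve quality of life and spiritual wellbeing".

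Under Primary endpoints, "Two primary endpoints are distinguished". The first is the general quality of life scale of the EORTC QLQ-C15-PAL. The other is introduced as "Second, spiritual wellbeing as measured by the subscale meaning/peace" of the FACIT-Sp-12.

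There is one sample size calculation. The analysis behind it: "We will conduct a mixed design measures ANOVA to detect differences between the control-group and the intervention-group over pre-, post- and follow-up measurement". Its settings: "To detect a small effect (effect size f = .10) with statistical power 80%, alpha 5" (per cent), with "a correlation between repeated assessments of r = .63, we need a sample of 122 patients". Then: "With an expected drop out of 20%, we will include 153 patients". The text does not say which endpoint the calculation serves, divides the 5% between no endpoints, and does not say whether one or both must be positive.

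**The concern.** A sample size for one test at the full 5% fits a trial with one deciding endpoint. This document names two and describes the primary aim in two ways, so it leaves open what a positive trial would be. The rule matters because each two-endpoint rule breaks one of the two stated operating characteristics. If a win on either endpoint suffices, the chance of a false positive trial exceeds 5%. If both are needed, the chance of success falls below 80%.

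The trial is non-blinded, its primary outcomes are self-reported, and the Discussion expects the intervention to be incorporated in guidelines. A rule chosen after the results are known would carry little weight. One possible outcome is a significant result on meaning/peace only: it would satisfy one of two named primary endpoints without answering the primary question in Methods/Design.

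**Working it through.** **Inputs from the Protocol article.** Groups k = 2; measurements m = 3; f = 0.10; correlation between repeated assessments 0.63; alpha 0.05; power 80%; 122 evaluable; 20% drop-out; 153 enrolled; 1:1 allocation.

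**Assumed.** The correlation r between the two endpoints is not given; the range 0 to 0.8 is shown. Power figures involving both endpoints take f = 0.10 on each.

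**Step 1: reproduce the plan's figure.** For the group-by-time interaction:

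- lambda = f² × N × m / (1 − 0.63) = 0.01 × 122 × 3 / 0.37 = 9.89
- df1 = (k − 1)(m − 1) = 2; df2 = (N − k)(m − 1) = 240
- Power from the noncentral F distribution: 80.6% at N = 122 and 79.9% at N = 120. The minimum N is 121, or 122 with equal arms.
- Enrolment: 122 / 0.80 = 152.5, rounded up to 153.

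Both figures agree with the plan. A between-groups main effect would need 594, so the plan was sized on the interaction, for one endpoint at the full 5%.

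**Step 2: the error rate if either endpoint counts at 5%.** Under independence, 1 − 0.95² = 0.0975. Correlated cases come from simulating two 2-df F tests (table).

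**Step 3: power if both are required at 5% each.** Under independence, 0.806² = 0.649. Correlated cases are simulated in the same way.

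| Assumed r | Either rule: error | Either rule: power | Both rule: power |
|---|---|---|---|
| 0 | 9.8% | 96% | 65% |
| 0.3 | 9.5% | 94% | 67% |
| 0.5 | 9.2% | 92% | 69% |
| 0.7 | 8.5% | 89% | 72% |
| 0.8 | 8.0% | 88% | 73% |

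Under the both rule the false-positive rate does not exceed 5%, because a false claim requires a significant result on an endpoint with no effect, tested at 5%.

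**Step 4: what would restore the failing figure.**

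- *Either rule, 2.5% per endpoint.* Power per endpoint at N = 122 falls to 71.9%. Power for at least one endpoint is about 92% (r = 0) to 81% (r = 0.8). For 80% per endpoint, 144 evaluable are needed: 144 / 0.80 = 180 enrolled.
- *Both rule.* 80% joint power needs about 155 evaluable at r = 0 (155 / 0.80 = 193.75, so 194 enrolled), about 150 at r = 0.5 (188 enrolled) and about 144 at r = 0.7 (180 enrolled).
- *Quality of life alone decides, or is tested first in a fixed sequence.* No change: 5% and 80.6% hold at 122 evaluable and 153 enrolled.

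**The case against.** The strongest objection is that a multiplicity or success rule usually belongs in the statistical analysis plan or the full protocol, neither of which is shown, and that a journal article condenses. This stands as far as it goes: the absence of a rule here is not the finding. What remains is in the printed text: two incompatible statements of the primary aim, and a calculation for one undivided test beside two primary endpoints. A later plan that required both endpoints, or split the alpha, would contradict the printed power for the rule it chose.

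A reader might infer more than the document supports, in three ways.

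- *That 5% and 80% both fail however success is defined.* They do not. The either rule breaks only the 5%, the both rule breaks only the 80%, and neither fails if quality of life decides.
- *That the trial will be called positive on meaning/peace alone.* No section states an either rule. The sample size section joins the two outcomes with a conjunction, as do the discussion part of the Abstract and the Discussion section. That leans towards requiring both, without settling it.
- *That the error rate is almost double.* That describes values near independence. Under Primary endpoints the article reports a significant relation between the FACIT-Sp-12 and quality of life. It gives no magnitude, but zero correlation is then the least natural case. At r = 0.8 the error is about 8%.

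It is also fair to object that the preferred remedy favours Methods/Design over the two-outcome aim and has its own power cost. That stands and is counted under the fix.

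**Conclusion.** The point holds in this limited form. The primary aim is stated inconsistently, and the sample size matches only the version in which one endpoint decides or leads a fixed sequence. Under an either rule at 5% each, the trial-level error is about 8 to 9.8% instead of 5%. Under a both rule, power is about 65 to 73% instead of 80%.

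The error figures rest on an assumed between-endpoint correlation of 0 to 0.8; the joint power figures also rest on f = 0.10 for both endpoints. The direction of each shortfall is the same across the whole range. The single-endpoint calculation itself is correct.

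**What to change.** Reconcile the primary aim across the Abstract, Background, Methods/Design, Primary endpoints and Sample size calculation, and state the success rule before any analysis.

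**Preferred: a fixed sequence.** Test QLQ-C15-PAL general quality of life first at two-sided 5%. Test FACIT-Sp-12 meaning/peace at 5% only if the first is significant; otherwise report it descriptively. This holds the overall error at 5%: if quality of life has no effect, any false claim must first pass a 5% test; if it has one, meaning/peace is the only possible false claim, again at 5%. The 122 evaluable, 153 enrolled and stated 80% then apply to quality of life. The change is one of wording. Its cost is that a meaning/peace claim becomes conditional on the quality-of-life result. Its power equals the joint power, about 65 to 73% if both effects are f = 0.10, and this should be stated.

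**If either endpoint is to count:** use Holm, or Hochberg where its assumption of positive dependence is acceptable, and restate the power. Per endpoint it is 72% when tested at 2.5%; for at least one endpoint it stays at about 80% or more if both effects are f = 0.10.

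**If both are to be required:** keep 5% for each and either state the joint power of about 65 to 73% or enlarge the trial to the sizes in Step 4.
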